| Follow-up                    | All participants will be followed for a total of 28 days.                                                                                                                                                                                                                                                                                                                                                                                                                                                                                                                                                                                                                                                                                                                                                                                                                                                                                                                                                                                                                                                         |
| Informed Consent             | Explicit written, signed informed consent from the subject or legally authorized representative will be obtained prior to any protocol specific procedures                                                                                                                                                                                                                                                                                                                                                                                                                                                                                                                                                                                                                                                                                                                                                                                                                                                                                                                                                        |

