### **4. STUDY PROCEDURES**

#### **4.1 Summary of study treatment**

All eligible ICU patients will be enrolled as soon as possible after fulfilling the criteria for randomization. Patients will be allocated in a 1:1 ratio to either the treatment group, receiving Xuebijing Injection, or to control group, receiving placebo.

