| The change in APACHE II score on day 6                                                  | The change in APACHE II score from baseline score measured at randomization to the score at Day 6 |

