## **7. DATA MANAGEMENT**

### **7.1 Data Collection Methods**

All data will be collected by trained staff at each study site using a case report form (CRF) worksheet developed by the coordinating centre. Data will then be entered into the web database (electronic case report form [eCRF]). Randomized patients will be followed up to death or 28 days post-randomization whichever occurs first. Study day 0 commences on randomization and concludes at the expiry of the calendar day. Data collection will be restricted primarily to those variables necessary to define clinical patient characteristics including: baseline demographics, primary diagnoses, physiological parameters, diagnostic interventions, therapeutic interventions and documentation of deaths and other SAEs.

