## **8. STATISTICAL CONSIDERATIONS**

### **8.1 Power Calculation and Sample Size**

Based on the previous observational CHESS study conducted in China, a 28-day all-cause mortality rate of 24.3% in the placebo group was assumed in this trial. With a dropout rate of approximately 15%, a sample size of 1800 patients provided 80% power at the two-sided 0.05 significance level on an assumption of an absolute risk reduction of 6% in mortality.

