### **8.2 Analysis of Results**

A senior statistician at Dongzhimen Hospital will perform data analysis on an intention-to-treat basis. Summary statistics will be used to describe the clinical data and presented as mean  $\pm$  SD, or percentages as appropriate. Continuous variables will be compared using a two-sample t-test or Wilcoxon rank-sum test if data show serious deviations from a normal distribution. Categorical data or ordinal data will be compared using a Wilcoxon rank-sum test, chi-square test or Fisher's exact test, as appropriate. All tests will be two-sided. Statistical significance declared for probability values of 0.05 or less. Analysis of the outcome of excluded patients due to other trials etc. will be in accordance with the CONSORT guidelines.

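### Section 8.2 lists only unadjusted tests for categorical outcomes, so the 28-day mortality comparison would forgo precision available from the SOFA stratum, age and baseline APACHE II

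*Protocol*

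**What the plan says.** The only analysis text is protocol section 8.2. For non-continuous outcomes it states: "Categorical data or ordinal data will be compared using a Wilcoxon rank-sum test, chi-square test", or Fisher's exact test, as appropriate. The analysis is by intention to treat with two-sided tests. No regression model, covariate or stratified test is mentioned, and the paragraph does not single out the primary outcome. That outcome, 28-day all-cause mortality (section 5.1), is binary.

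Three kinds of baseline information are available by design:

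- Section 4.3 stratifies randomisation by SOFA score, 2–7 against 8–13.
- Section 5.2 uses a baseline APACHE II score for two secondary outcomes, for example "The change in APACHE II score from baseline score measured at randomization to the score at Day 6".
- Section 7.1 lists "baseline demographics, primary diagnoses, physiological parameters" among the data to be collected. Age is also an eligibility criterion (section 3.3).

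Section 8.1 sets out the planning assumptions: "a 28-day all-cause mortality rate of 24.3% in the placebo group was assumed in this trial", with the test "at the two-sided 0.05 significance level on an assumption of an absolute risk reduction of 6% in mortality". It concludes: "With a dropout rate of approximately 15%, a sample size of 1800 patients provided 80% power".

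**The concern.** The design treats baseline severity as prognostic, since it stratifies on SOFA, but the stated tests use no baseline information. When baseline variables predict death, adjusting for them removes variation that has nothing to do with treatment. The confidence interval for the same absolute risk difference becomes narrower, and the result depends less on a chance imbalance in age or severity. Here the information is collected for other purposes, so the gain needs no extra patients. The cost of leaving it unused is a somewhat larger chance of missing a true effect in a trial with one primary comparison planned at 80% power.

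**Working it through.** **Inputs.** From section 8.1: control risk 0.243, absolute reduction 0.06 (so treated risk 0.183), two-sided 0.05, 80% power, 15% dropout, total 1800. From section 4.1: 1:1 allocation. Evaluable patients: 1800 × 0.85 = 1530, or 765 per arm.

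**1. Reproduce the plan's figure.** The unadjusted two-proportion formula, with mean risk 0.213, is

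n = [1.96·√(2·0.213·0.787) + 0.842·√(0.243·0.757 + 0.183·0.817)]² / 0.06² ≈ 730 per arm.

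The continuity correction, n/4·[1 + √(1 + 4/(n·0.06))]², gives 763 per arm, or 1526 in total. Dividing by 0.85 gives 1796, which matches 1800. Without the correction the total is 1460/0.85 ≈ 1718. The trial is therefore sized for an unadjusted comparison. At 1530 evaluable patients the power is 80.1% with the correction and 81.8% without it.

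**2. Unadjusted precision at 765 per arm.**

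SE = √[(0.243·0.757 + 0.183·0.817)/765] = √(0.33346/765) = 0.02088.

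The 95% CI half-width is 1.96 × 0.02088 = 0.041, or 4.1 points. Power is Φ(0.06/0.02088 − 1.96) = Φ(0.914) = 82.0%.

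**3. Effect of adjustment.** The protocol gives no prognostic strength, so this step rests on an assumption. I took one standard-normal prognostic index standing for all the covariates together, with logistic slopes 0.5, 0.8, 1.0 and 1.2 and marginal risks held at 24.3% and 18.3%. The variance ratio v is the variance of the standardised risk difference divided by the unadjusted variance. Power is Φ(0.06/(0.02088·√v) − 1.96), half-width is 4.09·√v points, and the equivalent evaluable number is 1530/v.

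| Assumed AUC | v | Power | Half-width (points) | Equivalent evaluable N |
|---|---|---|---|---|
| none | 1 | 82.0% | 4.1 | 1530 |
| 0.63 | 0.960 | 83.5% | 4.0 | 1594 |
| 0.70 | 0.906 | 85.5% | 3.9 | 1689 |
| 0.74 | 0.863 | 87.1% | 3.8 | 1773 |
| 0.78 | 0.819 | 88.8% | 3.7 | 1868 |

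As a cross-check, 3000 simulated trials per setting at N = 1530 compared the unadjusted chi-square test with a covariate-adjusted logistic test. The unadjusted power was 81–82%. The adjusted power was 83.5%, 85.0%, 86.6% and 88.5% for AUC of about 0.64, 0.69, 0.74 and 0.79.

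**4. How much comes from the SOFA stratum alone.** Take the same index, an assumed correlation of 0.5 to 0.9 between SOFA and the index, and 30–50% of patients in the upper stratum. The two-level stratum then yields about 15% (correlation 0.5), 30% (0.7) or 50% (0.9) of the variance reductions above. What age and APACHE II add beyond the stratum is the remainder.

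**The case against.** The strongest case against is that nothing here is wrong. The sample size and the listed tests agree with each other, the test is valid, and the planned power is met. Ignoring the stratum makes the test slightly conservative at most. This stands in full: a reader might infer an invalid analysis or an underpowered trial, and step 1 of the working shows neither.

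It can also be said that section 8.2 is a generic paragraph and that covariates are usually left to the SAP, which was not available here. This stands in part. A reader might infer that the protocol expressly assigns the primary outcome to an unadjusted test or rules out adjustment. It does neither; the reading is an inference. But section 8.2 does state methods, its only ones for a binary outcome are unadjusted, and the sizing matches them. This is a stated choice that could be better, not just missing detail.

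Third, the gain is hypothetical. This stands. The low end is only about 1.5 points of power. The eligibility limits (age at most 75, SOFA at most 13, exclusion of severe liver or kidney dysfunction) may weaken the predictors, and APACHE II already contains age points, so age may add little separately.

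Three further inferences are not supported:

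- That most of the variation in death is predictable at baseline: the assumed range removes only 4–18% of the variance.
- That the SOFA stratum carries little of the information: it could supply about half of the gain.
- That baseline APACHE II exists for every patient: the synopsis ties randomisation to the baseline SOFA score, and completeness of APACHE II is not stated.

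**Conclusion.** The point holds as lost precision on the primary comparison. Relative to no adjustment at all, pre-specified use of the SOFA stratum, age and baseline APACHE II would add about 1.5 to 7 points of power at 765 per arm. This is worth about 64 to 338 extra evaluable patients (1594 − 1530 and 1868 − 1530), with no change in the quantity estimated.

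These figures rest on three assumptions: the section 8.1 risks, 15% loss, and a combined AUC between about 0.63 and 0.78, for which the protocol gives no source. The share due to the stratum also rests on assumed correlations, so the separate contribution of age and APACHE II is not determined. The change is worth making because it costs little, not because the present test would mislead.

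**What to change.** State in section 8.2 that the primary analysis of 28-day mortality is a logistic model with treatment, SOFA stratum (2–7 or 8–13), age and baseline APACHE II, the last two as continuous terms. Report it as a standardised (marginal) risk difference with 95% CI. This keeps the result on the absolute scale of section 8.1; the model's odds ratio would be conditional on the covariates and would not answer the same question.

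Fix the covariates before unblinding, use simple imputation for rare missing baseline values, and keep the unadjusted comparison as a supporting analysis. If a SAP already specifies adjustment, bring section 8.2 into line with it.

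The cost is a few sentences and a few lines of code, with no new data. The small downside is that the covariates must be named in advance and baseline APACHE II must be near complete, which the change-score outcomes in section 5.2 need anyway.

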| Secondary outcome            | 
 
1) In ICU mortality
 
2) In hospital mortality
 
3) Length of stay (LOS) in the ICU
 
                                                                                                                                                                                                                                                                                                                                                                                                                                                                                                                                                                                                                                                                                                                                                                                                                                                                                                                                                                      |

|                       |                                                                                                                                                                                                                                                                                                                                                                        |
|-----------------------|------------------------------------------------------------------------------------------------------------------------------------------------------------------------------------------------------------------------------------------------------------------------------------------------------------------------------------------------------------------------|
|                       | 4) LOS in hospital, 28-day cumulative mechanical ventilation-free days
5) 28-day ICU-free days
6) The change in SOFA score on day 3
7) The change in SOFA score on day 6
8) The change in Acute Physiology and Chronic Health Evaluation (APACHE) II score on day 3
9) The change in APACHE II score on day 6 |

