### 5. OUTCOMES

#### 5.1 Primary outcome

##### 28-day all-cause mortality

Twenty-eight (28) day mortality is the most commonly used measure by scientific and regulatory authorities to assess efficacy of treatment of sepsis, and that will be the primary outcome of the study.

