#### 5.2 Secondary outcomes

| Secondary outcomes                                 |                                                                                                                      |
|-----------------------------------------------------------|----------------------------------------------------------------------------------------------------------------------|
| ICU mortality,                                     | The proportion of patients who had died to ICU discharge                                                             |
| Hospital mortality                                 | The proportion of patients who had died to hospital discharge                                                        |
| Length of stay (LOS) in the ICU                    | The total duration of stay in the ICU for the first 28 days after randomization                                      |
| LOS in hospital                                    | The total duration of stay in the hospital for the first 28 days after randomization                                 |
| 28-day cumulative mechanical ventilation-free days | The total number of days a patient was alive and not on mechanical ventilation support from randomization to 28 days |
| 28-day ICU-free days                               | The number of days alive and free of ICU from randomization to 28 days                                               |
| The change in SOFA score on day 3                  | The change in SOFA score from baseline score measured at randomization to the score at Day 3                         |
| The change in SOFA score on day 6                  | The change in SOFA score from baseline score measured at randomization to the score at Day 6                         |

|                                                                                                |                                                                                                   |
|------------------------------------------------------------------------------------------------|---------------------------------------------------------------------------------------------------|
| The change in Acute Physiology and Chronic Health Evaluation (APACHE) II score on day 3 | The change in APACHE II score from baseline score measured at randomization to the score at Day 3 |

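### The single 0.05 significance rule in section 8.2 is not limited to the primary outcome, so any of ten overlapping secondary outcomes can be declared significant even if 28-day mortality is neutral

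*Protocol*

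**What the plan says.** Protocol section 8.2 describes the analysis in one paragraph. It assigns t-tests or Wilcoxon rank-sum tests to continuous variables, and rank-sum, chi-square or Fisher tests to categorical or ordinal ones. It then says "All tests will be two-sided" and, as a separate sentence, "Statistical significance declared for probability values of 0.05 or less". The paragraph does not name the primary outcome, rank the outcomes, or make a secondary claim depend on the primary result.

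Section 5.1 names one primary outcome, 28-day all-cause mortality: "that will be the primary outcome of the study". Section 8.1 sizes the trial on that outcome alone, at two-sided 0.05.

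Section 5.2 defines ten secondary outcomes, beginning with ICU mortality ("The proportion of patients who had died to ICU discharge") and ending with "The change in APACHE II score from baseline score measured at randomization to the score at Day 6". The synopsis numbers only nine because its fourth item holds two: "LOS in hospital, 28-day cumulative mechanical ventilation-free days".

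**The concern.** The protocol is not silent on significance. It fixes a rule, and the rule is wider than the design supports. The trial is planned around one mortality comparison, yet the wording gives a length of stay or a day-3 severity score the same right to be called significant.

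Suppose 28-day mortality is neutral. A report that follows section 8.2 to the letter could still declare significance on one or more secondary outcomes, with nothing in the protocol marking that declaration as weaker evidence.

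The overlap makes this worse for interpretation. ICU length of stay is "The total duration of stay in the ICU for the first 28 days after randomization", and ICU-free days is "The number of days alive and free of ICU from randomization to 28 days". They cover the same 28 days, so one chance imbalance can give two significant results that look like mutual confirmation. ICU with hospital mortality, and each severity score measured at two days, overlap in a similar way.

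**Working it through.** **1. The plan's own figure.** Section 8.1 gives 24.3% mortality on placebo, a 6-point absolute reduction (so 18.3%), two-sided 0.05, 80% power, about 15% dropout and 1800 patients. With mean rate 0.213:

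n per arm = [1.960·√(2·0.213·0.787) + 0.842·√(0.243·0.757 + 0.183·0.817)]² / 0.06² = 730.

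The continuity correction raises this to 763 per arm, or 1526 in all. Then 1526/0.85 = 1796 after rounding up to an even number, which reproduces 1800. Without the correction the total is 1460/0.85 = 1718. The sample size therefore rests on the primary outcome only. The protocol states no error rate for the secondary outcomes.

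**2. Does the 0.05 rule reach the secondary outcomes?** The primary outcome is binary. The t-tests and rank-sum tests in the same paragraph are for continuous or ordinal data, so they must serve other variables. Lengths of stay, free days and score changes are such variables. The threshold follows with no restriction, so the natural reading is that it applies to them.

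**3. How many outcomes?** Two mortality measures, two lengths of stay, two kinds of free days, and SOFA and APACHE II change at days 3 and 6: 2 + 2 + 2 + 4 = 10.

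**4. Chance of at least one declaration with no true effect on any of the ten.** For independent tests:

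- either direction: 1 − 0.95¹⁰ = 0.401
- in favour of Xuebijing: 1 − 0.975¹⁰ = 0.224

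For correlated tests, take ten standard normal statistics, each signed so that positive favours Xuebijing, with common correlation ρ and c = 1.96:

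P(any |Z| > c) = 1 − ∫ φ(x)·[Φ((c − √ρ·x)/√(1−ρ)) − Φ((−c − √ρ·x)/√(1−ρ))]¹⁰ dx.

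The one-direction figure drops the second Φ term. The protocol gives no correlations, so every ρ is an assumption.

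| Assumed ρ | At least one, either direction | At least one favouring Xuebijing |
|---|---|---|
| 0 | 40.1% | 22.4% |
| 0.3 | 35.1% | 17.8% |
| 0.5 | 28.7% | 14.4% |
| 0.7 | 21.3% | 10.7% |
| 0.8 | 17.3% | 8.6% |
| 0.9 | 12.8% | 6.4% |

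**5. An uneven correlation pattern.** Group the outcomes as two mortality measures, four stay or free-day measures and four score changes. Simulation with 400,000 draws gives, for either direction:

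| Correlation within groups | Correlation between groups | At least one |
|---|---|---|
| 0.5 | 0.2 | 33.9% |
| 0.7 | 0.3 | 28.8% |
| 0.8 | 0.5 | 23.5% |
| 0.9 | 0.7 | 17.5% |

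These lie inside the range in step 4.

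**The case against.** The strongest objection is that multiplicity belongs to the SAP. Testing order, adjustment and the supportive status of secondary outcomes are commonly left there, the SAP is not at hand, and a general 0.05 threshold does not forbid a hierarchy. This stands in part: the absence of an adjustment procedure from the protocol is not an error, and this point does not claim that it is. The point is that the protocol states an unrestricted rule. An SAP that treated the secondary outcomes as supportive would have to depart from that sentence, and the two documents would then carry different rules.

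A second objection is that the words about all tests belong to the sentence on sidedness, while the threshold sentence names no set of tests. That is correct. The broad reading comes from the content of the paragraph (step 2), not from an explicit statement.

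A reader might infer two stronger things, and neither is supported. One is that a significant secondary outcome would make this a positive trial. Section 8.2 only says when a result is called significant; the protocol has one objective and one primary outcome, both 28-day mortality. The other is that the primary test is compromised. It is planned at two-sided 0.05, and secondary tests do not alter its type I error.

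It is also fair to say that nominal reporting of secondary outcomes beneath a clear primary is an accepted convention. But then the protocol should call the results nominal, which it does not.

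**Conclusion.** The point holds as a matter of the standing of secondary claims. Section 8.2 as written allows a declaration of significance on any of ten overlapping outcomes, whatever the mortality result. With no true effect on any of them, the chance of at least one declaration is about 13% to 40% for assumed common correlations from 0.9 down to 0. In favour of Xuebijing it is about 6% to 22%.

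The 40% should not be read as the expected value: it assumes independence, and these outcomes overlap. Nor is any row of the table a firm lower limit, because the correlations are unknown. Even at 0.9 the either-direction figure is more than twice the nominal 5%. This is a cheap improvement worth making, not a flaw that threatens the primary conclusion.

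**What to change.** Limit the sentence in section 8.2 to the primary outcome, for example:

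> Statistical significance will be declared for 28-day all-cause mortality at two-sided 0.05. Secondary outcomes are supportive and will be reported as estimates with 95% confidence intervals, without claims of statistical significance unless the SAP prespecifies a multiplicity procedure.

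Whether to have such a procedure, and which, can be left to the SAP. One option is to test the ten with a Holm adjustment only after a significant primary result. For scale, a plain Bonferroni split tests each at 0.05/10 = 0.005, which holds the familywise error at or below 5% under any dependence (1 − 0.995¹⁰ = 4.9% if independent).

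The cost is one sentence and fewer secondary significance claims. The sample size of 1800, the data collected and the primary analysis do not change.
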